### Ethical Considerations

The study received ethical approval from the UW Human Subjects Division (STUDY 00010387). A waiver of informed consent was granted by the UW Human Subjects Division for baseline data collection and time and motion procedures, as no identifiers were obtained. Study staff performed consent procedures and obtained informed written consent for study participants in Aims 1‐4. To protect participant data, participants from Aims 1‐4 were assigned a study ID, and their study data was stored in connection with that ID. A separate linking survey connected their study ID to their medical record number, which was used to obtain prospective data. A Human Subjects Division–approved Data Safety and Monitoring Plan was used to ensure protective measures to safeguard participant information, including appropriate levels of training for staff, limited data access, secure digital and physical storage places, and data transmission. Madison Clinic participants initially received a US $20 cash incentive and a US $5 meal voucher. Participants at the Center initially did not receive an incentive, but this was amended in April 2023 to provide a US $25 online gift card for consistency between sites. To help boost enrollment, the participation incentive was increased to US $40 in cash and a US $5 meal voucher for participants at Madison Clinic in August 2023. Participants who completed the additional acceptability survey were provided a US $10 electronic gift card upon survey completion. Participants who participated in the interview were provided a US $40 electronic gift card. In August 2024, we began offering incentives in cash as participants noted lack of email access as a barrier for survey and interview participation.

## Results

During the baseline data period of January 2019 to December 2021 at the Center, 6906 unique clients were seen for 8492 HIV and STI testing visits, and 272 clients had 612 PrEP visits (Table 2). Most clients (n=5703, 79.5%) were cisgender men. Almost half were White (n=3452, 48.1%). Nearly one-third (n=2185, 30.4%) reported no insurance. Among testing visit clients, about 86% (n=5937) were HIV negative (though HIV status was missing or unknown for 11.5% [n=794]), of whom, 15.6% (n=929) reported being on PrEP. About 2.5% (n=175) of testing visit patients were living with HIV, and about one-third of those clients reported that they were on ART (n=55, 31.4%), though data were missing for most clients (n=105, 60%).

At Madison Clinic during the same baseline period (Table 3), there were 117 unique patients seen for nPEP, 328 unique patients seen for HIV testing visits, and 400 unique patients seen for PrEP visits. There were 146 patients who tested positive for HIV for the first time and 511 patients with HIV whose viral load was detectable (>40 copies/mL) at some point during that time (Table 4). Among patients seen, 48.1% were White (n=722), 18.4% were Black or African American (n=276), 7.9% were Asian (n=119), and 7.1% were Hispanic or Latinx (n=106). Most (77.6%) were male (n=1065), 22.2% were female (n=334), and only 0.2% were transgender or nonbinary (n=3).

During study enrollment from January 2022 to December 2024, 733 unique people completed 753 GAIN study research visits (Tables 2-4). Of those visits, 491 visits were completed by 489 participants seeking HIV testing and/or PrEP at the Center. Most of those participants were seeking HIV testing (96%), were cisgender men (333/489, 68.1%), were White (278/489, 56.9%), with a median age of 30 (IQR 25‐35) years. About one-quarter (123/489, 25.2%) were currently on PrEP. Seven people with HIV seeking STI testing were enrolled from the Center. These participants were all cisgender men, most were White (n=7, 71.4%), with a median age of 57 (IQR 41‐61) years. Of those participants, 1 was not taking ART but had previously, the other 6 were currently taking ART.

At Madison Clinic, 61 visits were completed by 43 participants seeking HIV testing, nPEP, and/or PrEP. The majority of participants were there for a PrEP persistence visit (n=26, 60.5%). Most of these participants were cisgender men (n=37, 86%) and White (n=27, 62.8%), with a median age of 35 (IQR 31‐44) years, and most (n=30, 69.8%) were on PrEP. At Madison Clinic and MOD Clinic, 194 people with HIV seeking care were enrolled during the same time period. These participants were mostly cisgender men (n=144, 74.2%); 43.3% (n=84) were White, 27.3% (n=53) were Black or African American, and their median age was 44.5 (IQR 35‐57) years. Among Madison and MOD Clinic participants with HIV, 69.1% (n=134) were currently taking ART and 32.5% (n=63) had a detectable viral load (>40 copies/mL) at the time of their study visit. Differences in the populations of participants at the Center and Madison Clinic reflect the different populations seen at the 2 sites.

As part of Aim 4 study activities (Table 5), during a recruitment period that included 228 study visits completed by participants seeking HIV and STI testing at the Center, staff invited 198 to take the postvisit acceptability survey, of whom 133 (67.2%) participants completed. During 6 study visits by PWH at the Center, staff sent participants 4 survey invitations, and 3 participants completed them (75% completion). Among 25 Madison Clinic participant visits for HIV and STI testing, nPEP, and PrEP, 10 of 21 invited participants completed the survey (47.6% completion). During 161 study visits for PWH at Madison and MOD Clinics, 47 of 77 (61%) invited participants completed the survey. Of those who completed the additional surveys, 21 participants seeking HIV and STI testing, nPEP, or PrEP from both sites and 20 people with HIV from both sites also participated in an in-depth interview. Only participants who completed the survey were invited to participate in interviews, and participation rates were at or below 50% for all groups. However, we stopped inviting eligible participants who were seeking HIV and STI testing, nPEP, or PrEP to the interview after we achieved saturation of themes.

**Table 5. T5:** Acceptability survey and interview completions for participants in the GAIN^a^ study from Seattle’s LGBTQ+^b^ Center and Madison Clinic.

Characteristic	Seattle’s LGBTQ+ Center		Madison Clinic		Total, n (%)
	Participants seeking HIV and STI^c^ testing, n (%)	Participants with HIV, n (%)	Participants seeking HIV and STI testing, nPEP^d^, and PrEP^e^, n (%)	Participants with HIV, n (%)	
Total study visits^f^	228 (47)	6 (86)	25 (58)	161 (83)	420 (57)
Survey invitations sent^g^	198 (86.8)	4 (66.7)	21 (84)	77 (47.8)	300 (71.4)
Surveys completed	133 (67.2)	3 (75)	10 (47.6)	47 (61)	193 (64.3)
Interviews completed	16 (12)^h^	1 (33.3)	5 (50)	19 (40.4)	41 (21.2)

a GAIN: Greater Access and Impact through Point-of-Care Nucleic Acid Test.

b LGBTQ+: lesbian, gay, bisexual, transgender, queer, and others.

c STI: sexually transmitted infection.

d nPEP: nonoccupational postexposure prophylaxis.

e PrEP: pre-exposure prophylaxis.

f Includes study visits during which participation in the acceptability survey was being offered

g Includes participants who were offered, agreed, and were eligible to be sent the acceptability survey at their study visit.

h Study staff stopped offering enrollment to all participants after thematic saturation was attained; therefore, not all eligible participants were invited.

Time-and-motion observations were made in 2021 for 25 total patients at Madison Clinic, 13 of whom were from the MOD Clinic (Table 6). We found that the median clinic visit time was 73 (IQR 54‐92) minutes. An additional set of time-and-motion observations, made in 2023 during a pause in study enrollment, included 22 total patients at Madison Clinic (10 of whom were from the MOD Clinic) and revealed a median clinic visit time of 64 (IQR 45‐88) minutes. This demonstrated that most patient visits were shorter than the amount of time the POC NAT used for the study would take to return a result (120 min). This finding led the study team to develop a protocol prioritizing recruitment of participants before their regular clinic visit to initiate the SAMBA test as soon as possible.

**Table 6. T6:** Total time observed in clinic (minutes), including waiting room time, during 1 observation period preenrollment (2021) and 1 period while enrollment was paused (2023).

Year and statistics	MOD^a^ Clinic	Madison Clinic	Total
2021, n	13	12	25
Range	46-301	19-155	19-301
Mean (SD)	93.5 (66.9)	66.8 (36.2)	80.7 (55.0)
Median (IQR)	74 (55-97)	64 (42-85)	73 (54-92)
2023, n	10	12	22
Range	32‐185	45‐95	32‐185
Mean (SD)	75.2 (43.6)	65.3 (17.2)	69.8 (31.6)
Median (IQR)	68 (61-74)	61 (51-80)	64 (45-88)

a MOD: Moderate Needs.

Test results data from Aim 1 participants at both the Center and Madison Clinic will contribute to a performance assessment of the SAMBA Qual, anticipated in 2027. For this analysis, we will calculate the overall specificity and sensitivity of the SAMBA II Qual whole blood test across all tested samples and at HIV-1 RNA thresholds of detectable (>40), 200, 400, 1000, 2000, and 3000 copies/mL. SAMBA performance will be compared to laboratory RNA test results. We hypothesize that the sensitivity and specificity of the SAMBA II Qual will be similar to those of laboratory-based pooled NAT.

Test results and longitudinal follow-up from Aim 3 participants at Madison Clinic will contribute to a survival analysis of time to undetectable viral load, as well as a performance assessment of the SAMBA Semi-Q, anticipated in 2026. We will report the limit of detection using the plasma HIV RNA level as the gold standard, and the agreement (kappa) between SAMBA and plasma HIV RNA levels, dichotomized at 1000 copies/mL and within the range of 1000 copies/mL ± 0.3 log.

For the survival analysis, we will report the time to an undetectable viral load by study arm. We calculated a sample size of 106 per arm, assuming a baseline of 40% of participants with an undetectable viral load, to detect a 20% increase in the proportion of participants with an undetectable viral among people with HIV at Madison Clinic, assuming a 20% loss to follow-up. We hypothesize that the SAMBA Semi-Q will have high agreement with the laboratory-based RNA testing, and that time to virologic suppression will be shorter among participants randomized to the POC NAT-tailored intervention compared with standard of care.

Data from Aim 4 will contribute to a paper on the acceptability of POC NAT among persons testing for HIV, anticipated in 2026 (Table 7). Another paper will address the acceptability of POC NAT among people with HIV using both qualitative data from interviews and participant survey responses, anticipated in 2026. Another paper using data collected as part of Aim 4 activities will explore HIV testing preferences using both the acceptability survey and interview data. We will use a convergent parallel mixed methods design for integration of qualitative and quantitative data. For the interview sample size, we planned to conduct 20 interviews each among the HIV testing group and people with HIV, or until saturation of themes. For surveys, a sample size of 100 HIV testing participants and 100 people with HIV was determined based on feasibility, the literature, and consultation with a choice-modeling expert. We hypothesize that more than 80% of participants surveyed will report a positive experience with POC NAT and that SAMBA implementation will be acceptable in community- and clinic-based settings. However, we hypothesize that the 2-hour TAT will be a limitation to the feasible implementation of POC NAT and that the semiquantitative nature of the test and the limit of detection of 1000 copies/mL may cause some hesitation in the use of the SAMBA Semi-Q.

**Table 7. T7:** Planned publication topics, analyses, and timelines.

Anticipated publication topics	Contributing aims and sites	Planned analysis	Target sample size	Attained sample size	Anticipated publication date
Performance of SAMBA Qual for HIV Testing	Aim 1, Seattle’s LGBTQ+ Center and Madison Clinic	Laboratory and POC^a^ NAT^b^ concordance	850 study visits	550 study visits	2027
Impact of POC NAT on time to undetectable viral load and SAMBA Semi-Q performance	Aim 3, Madison Clinic	Survival analysis, laboratory, and POC NAT concordance	212 study visits with up to 1-year longitudinal follow-up	194 study visits	2026
Acceptability of POC NAT among persons testing for HIV	Aim 4 interviews, Seattle’s LGBTQ+ Center and Madison Clinic	Qualitative	20 or until saturation of themes	21 interviews	2026
HIV testing preferences	Aim 4 interviews and surveys, Seattle’s LGBTQ+ Center and Madison Clinic	Qualitative, discrete choice analysis	20 or until saturation of themes, 100 surveys	21 interviews, 143 surveys	2026
Acceptability of POC NAT among patients with HIV	Aim 4 interviews and surveys, Madison Clinic and Seattle’s LGBTQ+ Center	Qualitative and descriptive statistics	20 or until saturation of themes,100 surveys	20 interviews, 50 surveys	2026
Time and motion	Patients at Madison Clinic and MOD Clinic	Rank-sum tests and flow analysis	10 visits per clinic per observation period	47 patient visits	2026

a POC: point-of-care.

b NAT: nucleic acid test.

Data collected as part of the time-and-motion component of the study will be the subject of a paper anticipated in 2026. We calculated a sample size of 20 participants during each observation period, assuming a mean visit duration without SAMBA of 66 minutes, an SD of 29, α=.05, 80% power, and that 50% of participants would be randomized to receive SAMBA Semi-Q testing. We hypothesize that the average clinic visit will be less than the 2-hour TAT of the POC NAT and that the impact of study procedures on clinic flow will be minimal.

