#### Recruitment Strategies

Participants were screened and approached regarding participation by study staff or provider referral. Patients at Madison Clinic could be called via phone in advance by study staff after chart review for eligibility, and patients at both sites were approached in the waiting room about study participation. A “priority score” was also developed using demographic and behavioral questions from a Center intake form for use in prioritizing clients at the Center for PrEP care and the GAIN study. Development and implementation of this priority score will be described separately.

For participants seeking HIV testing from the Center, we prioritized clients with a reactive POC antibody HIV test, those with any symptoms of AHI, and those who scored high on the priority score. For participants seeking HIV at Madison Clinic, we prioritized enrollment of patients seeking HIV testing and those seeking nPEP. Our recruitment target for these groups was 700 clients from the Center and 150 patients at Madison Clinic.

We aimed to recruit all people with HIV seeking STI testing at the Center. For people with HIV at Madison Clinic, we prioritized patients with low adherence and/or detectable viremia. Study staff attempted to conduct the study visit for these participants before their regular clinic visit, to initiate the POC NAT as soon as possible and maximize the chance that the participant might still be in clinic to receive their result in person. Our recruitment target for these groups was 50 clients at the Center and 212 patients at Madison Clinic.

Participants were invited during their study visit to participate in the extra survey and interview immediately after the study visit or on a later date. Our recruitment target for survey participation was 50 participants seeking HIV testing at each site and 50 people with HIV at each site. Our recruitment target for interview participation was 20 total participants seeking testing (at either site) and 20 total participants with HIV (at either site).

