Study staff collected specimens for all research tests and, if possible, any clinically indicated laboratory tests. HIV testing participants completed standard-of-care HIV testing as part of their visit at both sites, which could include the INSTI HIV-1/HIV-2 Antibody Test (bioLytical Laboratories, Inc) on a fingerstick specimen and/or the laboratory-based HIV-1/HIV-2 Combo enzyme immunoassay (Bio-Rad Laboratories, Inc). Reactive samples were confirmed using the Geenius HIV-1/2 Supplemental Assay (Bio-Rad Laboratories) with reflex testing via the RealTime HIV-1 viral load assay (Abbott Laboratories; for participants seen before November 2023) or the Cobas HIV-1 viral load assay (Roche Diagnostics; for participants seen in November 2023 and after), as appropriate. Laboratory testing was done at the Public Health–Seattle & King County Laboratory and the UW Virology Laboratory.

Initially, a 10 mL serum tube was collected for research HIV testing participants; in June 2023, this changed for participants at the Center to a 4 mL EDTA tube and a 6 mL serum tube to allow for running the SAMBA Qual on venipuncture blood and the laboratory testing on the serum tube. If all screening tests were negative, research laboratory testing also included a laboratory NAT pooled into a single 10-member pool and tested using the RealTime HIV-1 viral load assay (Abbott Laboratories; for participants seen before November 2023) or the Cobas HIV-1 viral load assay (Roche Diagnostics; for participants seen in November 2023 and after). If any screening HIV test was positive, a quantitative HIV-1 RNA test was performed. HIV-positive research participants at the Center had a 10 mL EDTA tube drawn for a laboratory NAT. For all research participants, pooled NAT or individual NAT was performed as the laboratory gold standard for backup of the non-FDA approved SAMBA test [46].

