## Discussion

### Principal Findings

The GAIN study was designed to assess the acceptability and feasibility of implementing POC NAT in community and clinical settings. This paper describes the protocol, the populations recruited into the study, and planned analyses. During 3 years of enrollment, the GAIN study conducted 552 visits with HIV testing participants at the 2 study sites. Enrollment of persons seeking HIV testing occurred predominantly at the Center due to the focus of its HIV/STI testing programs. During the same period, the study enrolled 201 people with HIV from both sites. Conversely, recruitment of people with HIV was predominantly from Madison Clinic. Recruitment for the qualitative components of Aim 4 included 193 total poststudy visit surveys and 41 in-depth interviews. At the Center, we found that transgender, nonbinary, and genderqueer people represented a greater proportion of our study population (23.9% of Aim 1 participants) compared with the baseline visits at the Center (11.9%). This may reflect changing demographics of clients at the Center due to shifting priorities of the organization combined with the prioritization of study recruitment among clients at highest likelihood of having HIV [47,48]. Among participants seeking HIV testing at the Center, 25.2% said they were currently on PrEP, which is significantly higher than in the baseline group of participants seeking HIV testing, of whom 15.6% reported being on PrEP. This could also be due to the study focus on recruiting clients who were high priority for PrEP, and could also be influenced by baseline data missingness, as 11.5% of the Center baseline participants did not have a recorded HIV status or PrEP status.

In the baseline population at the Center, 2.5% of clients were people with HIV. Based on that rate, we would expect approximately 50 clients with HIV to visit the Center annually. The GAIN study enrolled only 7 clients with HIV at the Center during the nearly 3 years of enrollment. This low enrollment could be due to some participants not identifying themselves as living with HIV when completing the Center’s intake form, preventing study staff from identifying all eligible clients for recruitment. Future studies may wish to further examine how POC NAT could be used among people with HIV seeking STI testing in a community setting.

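### Laboratory RNA is the only comparator named for SAMBA Qual accuracy, so any confirmed infection with undetectable RNA would drop out of a sensitivity figure presented as performance for HIV testing

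*Protocol article*

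**What the plan says.** The Results section of the protocol article plans overall sensitivity and specificity of SAMBA Qual "across all tested samples and at HIV-1 RNA thresholds of detectable (>40), 200, 400, 1000, 2000, and 3000 copies/mL". It then names the comparator: "SAMBA performance will be compared to laboratory RNA test results". No other comparator is given for this analysis. The hypothesis follows: "We hypothesize that the sensitivity and specificity of the SAMBA II Qual will be similar to those of laboratory-based pooled NAT".

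The section on study procedures for testing participants gives laboratory NAT the same standing: "pooled NAT or individual NAT was performed as the laboratory gold standard for backup of the non-FDA approved SAMBA test". It also shows that serology is available on these participants, by a point-of-care antibody test and/or a laboratory immunoassay: "Reactive samples were confirmed using the Geenius HIV-1/2 Supplemental Assay (Bio-Rad Laboratories) with reflex testing". Pooled NAT is run when all screening tests are negative, and an individual quantitative RNA test when any is positive.

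Aim 2 in the Introduction is worded as sensitivity, specificity and clinical outcomes. In Table 7 the topic is SAMBA Qual's performance in HIV testing, while the planned-analysis column calls the work concordance between laboratory and point-of-care NAT.

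**The concern.** Sensitivity for HIV testing should have infected people in its denominator. With laboratory RNA as the reference, the denominator is people with detectable RNA. Someone whose infection is confirmed by serology but whose RNA is undetectable counts as reference-negative. A negative SAMBA result in that person is a true negative, and a positive one is a false positive. The error in sensitivity can go only one way, upward.

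The study could have enrolled such people. At the Center, "we prioritized clients with a reactive POC antibody HIV test", and every positive screen leads to a quantitative RNA test, so the combination of reactive serology and undetectable RNA would be on record. To explain low enrollment of people with HIV at the Center, the Discussion raises the possibility of "some participants not identifying themselves as living with HIV when completing the" intake form. Undetectable RNA in a person with HIV is also not rare in this document: Table 4 reports 113 of 194 Madison Clinic participants with HIV (58.2%) below 40 copies. Those are patients in HIV care, so the figure shows that the state exists, not how often it occurs among testing participants.

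At stake is whether the report can answer Aim 2, or only says how well two RNA tests agree.

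**Working it through.** The plan states no figure that depends on the choice of reference, so there is none to reproduce. The check is 2x2 arithmetic plus a reading of the hypothesis.

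**1. Effect on sensitivity.** Let *s* be the share of RNA-positive infections that SAMBA detects, and *u* the share of all infections that are serologically confirmed with undetectable RNA. Assume SAMBA is negative in all of the latter. This fits the 400-copy detection limit cited in the study procedures, against the 40-copy laboratory cut-off. Then:

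- sensitivity against RNA = *s*
- sensitivity against infection = *s*(1 − *u*)
- overstatement = *s* × *u*

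The documents do not give *u*, so a range is shown:

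| *s* | *u* | Against RNA | Against infection |
|---|---|---|---|
| 1.00 | 0 | 100% | 100% |
| 1.00 | 0.10 | 100% | 90% |
| 1.00 | 0.20 | 100% | 80% |
| 1.00 | 0.40 | 100% | 60% |
| 0.90 | 0.20 | 90% | 72% |

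**2. The same in small counts.** Assume 3 RNA-positive participants, all detected, and *k* seropositive, RNA-undetectable participants, all missed. Sensitivity against RNA is 3/3 = 100%. Against infection it is 3/(3 + *k*): 75% for *k* = 1, 60% for *k* = 2, 50% for *k* = 3. Both the 3 and the *k* are illustrative.

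**3. Effect on specificity.** Take 491 + 61 = 552 testing visits and assume 10 infections, 4 of them RNA-undetectable, with 5 false positives.

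- Against infection: (542 − 5)/542 = 99.08%
- Against RNA: (546 − 5)/546 = 99.08%

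**4. The hypothesis.** It compares SAMBA's sensitivity and specificity with those of pooled NAT, so pooled NAT needs accuracy figures of its own. If laboratory RNA is the truth, pooled NAT in screen-negative participants is judged against itself and is right by construction. Screen-positive participants have an individual RNA test instead of pooled NAT. Nothing independent remains for SAMBA to be similar to.

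**5. The overall estimate.** The threshold list already starts at detectable RNA (>40). If RNA is the truth, the overall figure repeats that row. If it is meant to differ, it rests on a reference that the article does not name.

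**The case against.** The case on the other side is substantial, and much of it stands.

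- **RNA as sole reference.** A reader might infer that the plan declares RNA to be the only truth. It does not. RNA is the only comparator named, but the reference for the overall figures is not spelled out. The wording of the hypothesis, and the separate overall estimate, could imply another standard, and fuller documents may define one. This limits the point to what the article names. It does not remove the mismatch between that comparator, the hypothesis and the Table 7 topic.
- **RNA is legitimate for NAT-to-NAT agreement.** This stands. Table 7 already calls the analysis concordance, and SAMBA was added to standard-of-care serology, not used in its place. The difficulty arises only when the result is read as sensitivity for HIV infection.
- **No such participant is documented.** This also stands. Table 2 lists 489 of 489 Center testing participants as HIV negative. That may be status at enrollment, and Table 3 gives no HIV status for Madison Clinic, so the count is open and may be zero.
- **Carrying over the baseline share.** A reader might apply the Center's baseline HIV-positive share (175/6906 = 2.5%) to the enrolled group. The documents do not support this. The share counts all HIV-positive clients, not those with undetectable RNA. Aim 1 is described as a study of persons without HIV, and clients known to have HIV had a separate enrollment group. Nondisclosure is offered only as a possible reason for missed recruitment, not as evidence that such clients joined the testing group.
- **PrEP use.** The shares on PrEP (123/489 at the Center, 30/43 at Madison Clinic) do not show that anyone was seropositive with undetectable RNA.

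**Conclusion.** The point holds as a conditional one. With laboratory RNA as the only named reference, any serologically confirmed infection with undetectable RNA leaves the sensitivity denominator, and sensitivity for HIV infection is overstated by *s* × *u*. This assumes that SAMBA is negative in those participants. The amount cannot be derived from the documents and is zero if nobody of that kind was enrolled. It would be wrong to say that sensitivity is in fact overstated. Specificity is practically unaffected.

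One part does not depend on the count: with laboratory RNA as truth, the hypothesis about pooled NAT cannot be tested. That, together with the Table 7 topic, is reason enough to state the reference for the overall estimates before the analysis anticipated in 2027.

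**What to change.** 1. Keep the laboratory RNA comparison and all the copy-number thresholds, but label them agreement with laboratory RNA, in line with the concordance wording in Table 7.
2. Define the overall sensitivity and specificity against infection status from the algorithm already performed (antibody or antigen/antibody test, Geenius, RNA). Report them for both SAMBA Qual and laboratory NAT, pooled or individual as run. Because RNA is part of that algorithm, note that laboratory NAT is not independent of the reference for infections found by RNA only.
3. Compute specificity in participants who are uninfected by that algorithm.
4. List any seropositive, RNA-undetectable participants separately, with SAMBA result and PrEP or ART use. If there are none, say so.
5. State whether the HIV status in Table 2 is status at enrollment or final status.

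The cost is one extra table from results already collected, and a reported sensitivity that may be lower.
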